### Participant Recruitment and Eligibility Criteria

Parent-child dyads will be recruited from kindergartens in Guiyang, Guizhou Province, China, with the support of Sun Yat-sen University and Guiyang Preschooler Education College. The entire recruitment process will be school-based. Kindergarten teachers will be asked to send a message to the parents in their respective WeChat class group. The message will briefly introduce the objectives and significance of the study. Parents will respond “yes” or “no” regarding their intention or willingness to participate. Face-to-face meetings will be held to provide more details to those parents who agree to participate in the study, especially on measurements, and to clarify the benefits that parents will receive after the study. Parents will be asked to add the researcher’s WeChat and sign the informed consent at the end of parent meetings. The inclusion criteria are as follows: (1) parents are older than 21 years and have children aged 3-6 years (the age range from 3 to 6 years has been found to be a strong predictor of future health) [51], (2) parental commitment to participate in the overall 6-month intervention, (3) parents have access to mobile technology, (4) parents and children are healthy (referring to a state of physical, mental, social, intellectual, and emotional well-being and the absence of disease) based on a health assessment performed by the kindergarten on the commencement day of a new semester, and (5) parents reside with participating children for at least 4 days a week in order to adequately expose the children to the parent-based intervention.

### Randomization

Once participants are recruited and baseline measurements are collected, participants will be randomly allocated to either an intervention group (eHealth group) or a control group (traditional group) in a 1:1 ratio through a computer-generated list, using the statistical software SPSS (IBM SPSS 27, IBM Corp). The randomization will be conducted by a researcher who is blinded to the intervention recruitment and delivery. Random allocation to either the eHealth group or the control group will not be informed to parents.

### Theoretical Foundation

The intervention is grounded upon social cognitive theory (SCT), which considers learning as a social phenomenon that comes from a person’s interaction with others through watching and observing [52]. Moreover, it considers the evidence that eHealth implemented directly to preschoolers may have adverse impacts on preschoolers’ healthy lifestyles (eg, disturbed sleep, myopia, and increased screen time). Thus, a key component of this intervention is to involve parents in modeling health-promoting behaviors among their preschool-aged children. Figure 2 depicts how the intervention will be conducted. First, SCT proposes that an individual’s behavioral modification can be influenced by personal, environmental, and behavioral factors [53]. These 3 factors describe what intervention content should be involved to induce behavioral modification:

Personal factors refer to an individual’s self-efficacy to carry out a behavior, which is dependent on personality, knowledge, beliefs, self-perceptions, and expectations. Knowledge and beliefs of the importance of PA, DB, and sleep for preschoolers will be addressed through the topic content of the eHealth intervention (videos and reading materials).Environmental factors refer to supportive environments that help an individual to conduct a behavior. Interaction with others by posting photos, videos, and ideas concerning a healthy lifestyle will provide participants with vicarious learning. Communication, feedback, and reinforcement from other parents through social media platforms and from research staff through personalized interaction can provide parents with opportunities to practice the skills, potentially contributing to behavioral modification.Behavioral factors refer to the responses by the individual once they have practiced carrying out a behavior. The parent will put the skills and behaviors into practice after goal setting and action plans. Positive reinforcement will be gained by monitoring progress with the goals and action plans and the personal benefits experienced.

Additionally, the 4 processes for behavior change involved in SCT are attention, retention, reproduction, and motivation. If any one of these steps is missing, the learning and adaptation of new behaviors will not take place. These 4 steps describe what intervention sequence should be followed to induce behavioral modification:

Attention, which is matched with personal factors, represents that individuals cannot learn unless they pay attention to what is happening around them. Therefore, attention is tackled by providing printed educational materials and TikTok videos delivered through WeChat [54].Retention, which is matched with environmental factors, represents that individuals must not only recognize the observed behaviors but also remember these behaviors at some later time. Therefore, retention is addressed by interactions with other participants through the WeChat group to support parents in remembering the content of videos and educational material. Moreover, each week, parents will receive 4 push notifications to remind them about the information of each interactive component (ie, video or printed material, communication, goal setting, and feedback).Reproduction, which is matched with behavioral factors, represents that individuals must be physically and mentally capable of producing the observed behaviors. Therefore, reproduction will be achieved through goal setting based on the SMART (Specific, Measurable, Achievable, Relevant, and Time-bound) goal framework, action plans, and solutions to barriers.Motivation, which is matched with behavioral factors, relates to the interests and achievements of individuals regarding the tasks and activities being put in place. Therefore, motivation is addressed by creating cognitive dissonance with parents describing current behaviors and asking parents to identify the positive consequences and expectations as a result of performing the planned behaviors.

**Figure 2 figure2:**
[figure not shown]
SCT-based eHealth intervention. DB: dietary behavior; PA: physical activity; SCT: social cognitive theory; SMART: Specific, Measurable, Achievable, Relevant, and Time-bound; WHO: World Health Organization.

### Intervention Procedure

The eHealth intervention comprises 12 interaction modules, including PA (n=4), DB (n=4), and sleep (n=4). Each module will be rotated weekly to reduce the order effect on the outcome variables during the 12-week intervention period (ie, PA, diet, sleep, PA, diet…). Given that previous social media studies have indicated that 5 to 9 members in a group will produce the desirable group interactive effect [55], the participants will be grouped into 26 WeChat groups (8 members involved in each WeChat group) by the researchers according to the sample size calculation. Given that a facilitator has been found to be important to potentially make the intervention more individualized and may be successful in behavioral change [56], a teacher with expertise in PA, DB, and sleep who is working in the kindergarten will act as a facilitator, also known as a “captain,” in each WeChat group. Facilitators will be trained in a 5-hour workshop before the intervention and will be blinded to the study objectives. They will be responsible for sending videos; facilitating group interactions; responding to questions from parents; helping parents establish PA, diet, and sleep goals for their children; and providing feedback. Parents in each WeChat group will receive 2 self-monitoring text messages, and they will be required to provide a “yes” or “no” response. The first message will be sent as a feedback message to evaluate the progress toward the child’s weekly goal in the middle of the week. An “N” response may elicit a skill-building response to adjust the goal or adopt alternatives to achieve the goal (eg, try offering the same vegetable many times in different ways). If the parent responds “Y,” the facilitator will generate a message to reinforce positive behaviors, such as “Be proud of yourself, you’re getting your child off to a healthy start!” The second self-monitoring message will be sent on the weekend to assess goal attainment for the weekly target behavior before the new weekly theme is introduced. Figure 3 illustrates the intervention process of each module [57,58]. Multimedia Appendix 1 indicates what specific content will be shared.

Consistent with SCT [52], the content of each module will follow 4 steps (Figure 2 illustrates the intervention process of each module) as follows:

1. Attention (read educational material and watch a TikTok or Douyin 3-minute video): Each video involves behavior change techniques, which are mapped onto SCT and are critical for promoting behavior change [59-61]. It will be sent to parents at the beginning of each week, with each video containing information related to goal setting, action plan, feedback, monitoring, shaping knowledge, natural consequences, repetition and substitution, comparison of outcomes, reward and threat, antecedents, identity, and self-belief [54,59].

2. Retention (parent interaction): A meta-analysis assessing the psychological architecture and adherence factors of online interventions indicated that intervention adherence is more likely to be influenced by push factors, peer communications, and personal contact [62]. Parents will receive regular messages to remind them to watch videos and read text. Facilitators and researchers will regularly share questions and images related to the week’s topic, aiming to stimulate discussion among parents [30]. For example, “What is your child’s current PA pattern?” and “Do you read the ingredient label of food when buying?” It was anticipated that parents would gain the most benefit from actively participating (posting information or commenting) based on findings from previous studies on online health discussion groups, which have indicated that parents who wrote posts, commented, asked questions, and provided support to others achieved greater benefits than passive parents [63,64]. If there are parents in the WeChat group who do not post or share, they will receive a reminder message sent by the facilitator via WeChat privately.

3. Reproduction (set goals and conduct behaviors): The facilitator of each WeChat group will help parents set goals related to the weekly topic based on SMART principles [65]. Goals should be individualized and can be adjusted along with the child’s and parent’s progress in behavior changes. The facilitator of each WeChat group will inform the parents via private text messages on how to employ goal setting to help their children set PA, DB, and sleep goals. It is encouraged to share goal achievements with other members in the WeChat group or with the facilitator privately. Throughout the intervention period, parents will be offered the possibility to interact with the facilitator on a regular basis by means of WeChat in order to discuss problems and raise questions regarding the promotion of PA, a healthy diet, and sleep for their children.

4. Motivation (feedback and making changes): Feedback and subsequent revision of goals have been shown to be positively related to successful interventions of behavioral modification [66,67]. Tailored feedback will be provided by a research assistant with expertise in lifestyle (PA, DB, and sleep) based on the goal, barrier identification, and solution. The research assistant will assist parents to revise their weekly theme-related goal following the SMART framework [68].

**Figure 3 figure3:**
[figure not shown]
Intervention mapping process of each module based on the 4 steps of social cognitive theory. PA: physical activity; SMART: Specific, Measurable, Achievable, Relevant, and Time-bound.

### Control Group

Parent-child dyads assigned to this group will receive a weekly pamphlet on PA, DB, and sleep recommendations via the child, but they will not receive interactive components.

### Sample Size

A recent systematic review and meta-analysis indicated a small but significant effect size for interventions to improve the PA of children aged younger than 5 years [69]. Interventions that aimed to enhance DB and reduce sleep problems among preschoolers had small to medium effect sizes [9,70]. Based on the information, a priori analysis will be conducted using G*power 3.1.9.6 [71]. A minimum sample size of 82 parent-child dyads in the intervention and control groups separately is required to detect a small effect size (*d*) of 0.3 with a power of 0.80 under the condition of an α level of .05. Considering a 20% potential attrition rate, 206 parent-child dyads in total are needed.

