### Statistical Analysis

All statistical analyses will be conducted using IBM SPSS 27 (IBM Corp), and a 2-sided *P* value <.05 will be considered statistically significant. Baseline characteristics between the intervention group and control group will be compared using the chi-square test for categorical variables and ANOVA for continuous variables. A mixed model, which accounts for missing repeated measures, will be adopted with a 2-level between-group factor (intervention and control) and 2-level within-group factor (postintervention and follow-up assessment) repeated measures analysis of covariance (RM ANCOVA) to examine whether the eHealth-based parenting intervention improves preschoolers’ PA, DB, and sleep compared to the findings in the control group.

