## Results

Parent-child dyads were recruited in September 2023. Baseline and posttest data collection occurred from October 2023 to March 2024. The follow-up data will be obtained in June 2024. The research team has completed data collection for 238 parent-child dyads and is currently analyzing the outcomes. The results of the study are expected to be published in 2025.

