
This study has several strengths, including a randomized controlled trial design, calculation of sample size that ensures adequate statistical power, and objective and valid data collection methods for outcome measurements. Multiple lifestyle-related behaviors (ie, PA, diet, and sleep) are targeted in the intervention. The intervention delivery is grounded upon 4 behavioral modification steps included in SCT. A 3-month follow-up will determine whether the behavioral changes made during the intervention can be maintained. This study addresses many limitations summarized from previous studies, such as failure to either consider the imbalance of the intervention dose to bias the results or consider the sequence of the intervention contents to bias the results.

There are some limitations that need to be considered. The parent-child dyads that will be allocated to either the intervention or control group may be from the same school, and it is therefore possible that the intervention content may be contaminated. Thus, the outcome of this intervention may not be generalizable to preschoolers living in other cities in China. Owing to subjective measurements for the questionnaires, there is potential for parents to intentionally or unintentionally misreport; however, this is common in all free-living studies examining behavioral measures [96].

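### The stated inputs (d = 0.3, 80% power, alpha .05) do not yield 82 dyads per arm: a two-group comparison needs 176, and any power gained from the repeated-measures model rests on a correlation that is not stated

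*Protocol article*

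**What the plan says.** The Sample Size section of the protocol article reports a G*Power calculation: "A minimum sample size of 82 parent-child dyads in the intervention and control groups separately is required to detect a small effect size". The value printed for the effect is d = 0.3, and the calculation is specified "with a power of 0.80 under the condition of an α level of .05". It then allows for 20% attrition and arrives at 206 dyads in total. It names no test family, number of measurements or correlation.

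The Randomization section fixes 1:1 allocation. The Statistical Analysis section sets the level as two-sided (a P "value <.05 will be considered statistically significant") and plans a mixed-model repeated-measures ANCOVA with a between-group factor and a "2-level within-group factor (postintervention and follow-up assessment").

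The Results section says that the team "has completed data collection for 238 parent-child dyads". The Discussion lists among the trial's strengths a "calculation of sample size that ensures adequate statistical power".

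**The concern.** Cohen's d is the standardised difference between two group means. With d, power, alpha and allocation all printed, a reader can recompute the number per arm, and the printed number is less than half of what those inputs give.

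This is a figure that disagrees with its own inputs, which is different from detail left to a fuller document. It matters because this is the only stated basis for the size of the trial, and the Discussion relies on it. If the primary outcome, preschoolers' physical activity, shows no significant difference, readers will take the result as coming from a trial with 80% power for d = 0.3. The article as written does not support that reading.

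**Working it through.** **Inputs.** From Sample Size: d = 0.3 (so SD = 1 on this scale), power 0.80, alpha .05, 82 per arm, 20% attrition. From Randomization: 1:1. From Statistical Analysis: two-sided level, two post-baseline assessments (T2 at 12 weeks, T3 at the end of follow-up).

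**1. The attrition step reproduces.** 82 / 0.8 = 102.5, rounded up to 103 per arm, or 206 in total. Any fault lies in the 82.

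**2. The 82 does not reproduce.** The normal approximation is n per arm = 2(z_alpha + z_power)² / d².
- Two-sided: 2(1.960 + 0.842)² / 0.09 = 174.4, so 175. The exact noncentral t, which is what G*Power uses for independent means, gives 176.
- One-sided: 2(1.645 + 0.842)² / 0.09 = 137.4, so 138. Exact: 139.

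**3. What 82 per arm delivers, unadjusted at one time point.** The noncentrality is 0.3 × √(82/2) = 1.92 on 162 degrees of freedom. Power is 48.0% two-sided (60.6% one-sided). The d detectable with 80% power is 0.44 two-sided.

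**4. What the planned model could add.** The article gives no correlation, so r is an assumption here. Compound symmetry is also assumed: the same r between any two of baseline, T2 and T3. Adjusting for baseline multiplies the variance by
- T2 alone: 1 − r²
- average of T2 and T3: (1 + r)/2 − r²

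Power at 82 per arm for d = 0.3, two-sided:

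| r (assumed) | T2 factor | T2 power | T2/T3 average factor | Power, effect sustained |
|---|---|---|---|---|
| 0.3 | 0.91 | 52% | 0.56 | 72% |
| 0.5 | 0.75 | 60% | 0.50 | 77% |
| 0.6 | 0.64 | 66% | 0.44 | 82% |
| 0.7 | 0.51 | 76% | 0.36 | 89% |

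Reaching 80% needs r of about 0.73 for T2 alone, or about 0.56 for the average.

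**5. Repeated-measures settings in G*Power.** For two equal groups f = d/2, so d = 0.3 is f = 0.15. The noncentrality is N f² m / (1 − rho) for the within-between interaction and N f² m / (1 + (m − 1)rho) for the between-group test. N is the total and m the number of measurements. The target is N = 164.

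| Test | f | m | rho | Total N for 80% power |
|---|---|---|---|---|
| Interaction | 0.15 | 3 | 0.5 | 74 |
| Interaction | 0.15 | 2 | 0.5 | 90 |
| Between | 0.15 | 3 | 0.5 | 236 |
| Between | 0.15 | 2 | 0.5 | 264 |
| Interaction | 0.10 | 3 | 0.5 | **164** |
| Interaction | 0.10 | 2 | 0.5 | 200 |

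The row that returns 164 uses f = 0.10, which is d = 0.2, and three measurements. It matches neither the stated d nor the two-level time factor.

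**6. The number reported in Results.** If the 238 dyads split evenly and all contribute, there are 119 per arm. Unadjusted power for d = 0.3 is then 63%, and the detectable d is 0.36. With the same assumed r of 0.3-0.7, power is 68-90% for T2 alone and 87-97% for the sustained T2/T3 average.

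**The case against.** The strongest reply is that the article names no t-test. It plans a baseline-adjusted model over two assessments, so 176 per arm and 48% power describe an analysis that nobody proposed. This stands as a limit on the conclusion. A reader might infer that a true d of 0.3 would be missed about half the time. The documents do not support that: the planned model can do considerably better, and with r of about 0.56 or more and a sustained effect it reaches 80% at 82 per arm. The 238 dyads also exceed the planned 206.

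A reader might also infer that the authors entered f = 0.10 with three measurements. The exact match at 164 makes this plausible, but it is inference. Other settings reach 164 at f = 0.15 if the correlation is low: the three-measurement between-group test near rho = 0.19 and the two-level interaction near rho = 0.08. Nothing in the article points to these values either.

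Finally, G*Power settings can be left to a fuller document, so their absence alone is not an error. But d, power and alpha are printed with a number per arm that they do not give, and the Discussion cites that calculation as a strength. Unstated settings might explain the number; they do not make the printed statement correct.

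**Conclusion.** The concern holds in this form: the sample-size statement is wrong as written. On its printed inputs the requirement is 176 per arm two-sided (139 one-sided), not 82, and the unadjusted single-time-point power at 82 per arm is 48%.

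Whether the planned analysis has 80% power for d = 0.3 cannot be determined from the article. It depends on the primary contrast and on the unstated correlation. The 52-76% and 72-89% ranges rest on compound symmetry, r of 0.3 to 0.7 and, for the second, an effect that persists to follow-up. So the trial is not shown to be underpowered for its planned model, but the claimed 80% is not supported. The 20% attrition step is correct.

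**What to change.** Without enrolling more dyads:

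1. Correct the Sample Size section so that the effect measure (d or f, with its value), test family, number of measurements and correlation are those actually used and together return the number given. If the calculation does not match the two-level model in Statistical Analysis, say so.
2. State the power at d = 0.3 and the detectable effect for the planned primary contrast at the number actually enrolled, with the correlation labelled as an assumption and a range shown. The unadjusted reference at 119 per arm is 63% power and a detectable d of 0.36.
3. Qualify the Discussion's statement on adequate power to match.

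The cost is wording and a short recalculation. Design, enrolment and analysis do not change. The stated power may become less favourable, depending on the contrast and the correlation that can be justified.

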### Outcomes

Data collection will be conducted at baseline (1 week before the intervention; T1), 12 weeks postintervention (at the end of the intervention; T2), and at the end of the 12-week follow-up period (T3).

### Demographic Information

The following demographic information will be collected from parents: socioeconomic status (range of income, educational level, and occupational status), age, gender, and marital status.

The following demographic information will be collected from preschoolers: sex, age, weight, height, and BMI. Preschoolers’ weight will be measured with standard practices to the nearest 0.1 kg using calibrated measurement scales (Salter) and height will be measured using a stadiometer (SECA) to the nearest 0.1 cm. BMI will be calculated with height and weight measurements. As sibship size has been observed to influence parenting behaviors, the number of children in the household will be collected.

